## Abstract

**Background:**

Gastrointestinal (GI) cancer is frequently diagnosed in people of working age, and many GI cancer patients experience work-related problems. Although these patients often experience difficulties returning to work, supportive work-related interventions are lacking. We have therefore developed a tailored work-related support intervention for GI cancer patients, and we aim to evaluate its cost-effectiveness compared with the usual care provided. If this intervention proves effective, it can be implemented in practice to support GI cancer patients after diagnosis and to help them return to work.

**Methods/Design:**

We designed a multicentre randomized controlled trial with a follow-up of twelve months. The study population (*N =* 310) will include individuals aged 18–63 years diagnosed with a primary GI cancer and employed at the time of diagnosis. The participants will be randomized to the intervention or to usual care. ‘Usual care’ is defined as psychosocial care in which work-related issues are not discussed. The intervention group will receive tailored work-related support consisting of three face-to-face meetings of approximately 30 min each. Based on the severity of their work-related problems, the intervention group will be divided into groups receiving three types of support (A, B or C). A different supportive healthcare professional will be available for each group: an oncological nurse (A), an oncological occupational physician (B) and a multidisciplinary team (C) that includes an oncological nurse, oncological occupational physician and treating oncologist/physician. The primary outcome measure is return to work (RTW), defined as the time to a partial or full RTW. The secondary outcomes are work ability, work limitations, quality of life, and direct and indirect costs.

**Discussion:**

The hypothesis is that tailored work-related support for GI cancer patients is more effective than usual care in terms of the RTW. The intervention is innovative in that it combines oncological and occupational care in a clinical setting, early in the cancer treatment process.

**Trial registration:**

METC protocol number NL51444.018.14/Netherlands Trial Register number NTR5022. Registered 6 March 2015.

## Background

Patients with gastrointestinal (GI) cancer experience work-related problems at the time of diagnosis [1]. In general, cancer survival rates have been improving in recent years due to early detection via screening programmes and continuous improvements in treatment [2, 3]. The burden of the disease itself and the treatment not only negatively affects quality of life [4–6] in all its aspects, but also work participation [7], with the additional financial consequences this brings [8, 9]. Work participation is becoming increasingly important in today’s ageing society, meaning that the incidence of cancer in patients of working age is also increasing. Furthermore, the raising of the retirement age is expected to bring an additional increase in the number of cancer survivors in the working population.

It is important that cancer patients are able to return to work (RTW), because having a fulfilling work life is associated with a higher quality of life [10, 11] and provides much-needed income [12]. Most cancer survivors want to resume work after treatment, but regrettably, not all survivors are able to do so, because they experience various difficulties and treatment-related factors [1, 13, 14], or even become unemployed [15]. In addition to diagnosis and treatment, patients have to deal with physical, emotional and social problems such as fatigue, pain, cognitive deficits, anxiety and depression. These can impair social functioning and affect the patients’ ability to RTW [15, 16].

Relatively few studies have assessed the employment status of patients with GI cancer [17, 18] compared to well-studied diagnoses such as breast cancer [19, 20]. Besides work-related problems due to cancer, GI cancer patients can be confronted with specific GI cancer-related problems, such as eating, defecation or stoma problems, which can interfere with their work and for which they need support. Work-related problems are experienced both at the time of diagnosis and during treatment, but no work-related support (in the form of interventions) is provided nowadays in curative settings. Earlier research has shown that patients appreciate receiving information on their RTW in the early stages of cancer treatment [1, 21, 22]. It is therefore essential to have an in-hospital-based care programme to support the RTW process. Moreover, work-related problems can vary in severity, meaning that any such intervention should provide tailored support.

We have developed a tailored work-related support intervention for GI cancer patients. We aim to evaluate the cost-effectiveness of the tailored work-related support intervention as compared with usual care. If this intervention proves effective, it can be implemented in practice to support GI cancer patients, starting at diagnosis, during treatment and in the period after diagnosis and treatment to help them RTW.

### Objective

The objective of this paper is to present the design of a study that aims to evaluate the tailored work-related support intervention in terms of cost-effectiveness.

## Methods/Design

This study will take the form of a two-armed non-blinded multicentre randomized controlled trial (RCT), with a follow-up of twelve months (see Fig. 1). We will compare the tailored work-related support intervention with the control group receiving the usual care, which takes the form of standard psycho-oncological care. Data will be gathered using questionnaires at baseline, three, six, nine and twelve months. The CONSORT statement was used to report the design of this study [23].

### Study population

The study population (*N =* 310) will include individuals aged between 18 and 63 years, with a primary diagnosis of GI cancer (oesophagus, stomach, liver, pancreas, biliary, small intestine, colon or rectum cancer), treated with curative intent (no study restrictions for type of treatment), employed at the time of diagnosis (including self-employment) and being on sick leave as a result of work-related problems due to the cancer diagnosis. The exclusion criteria are: 1) patients who are unable to speak, read or write Dutch sufficiently; 2) patients who have a severe mental disorder or other severe co-morbidity; and 3) patients who are receiving primary treatment at another hospital.

### Recruitment of participants

Eligible patients will be recruited between May 2015 and July 2016. GI cancer patients will be asked to participate at the hospital where they are receiving their treatment. The oncologist or oncological nurse will check each patient’s eligibility by assessing the inclusion and exclusion criteria. During their first visit to the hospital where they are being treated, patients will be informed about the study by their oncologist or oncological nurse. The oncologist or oncological nurse will then provide the patient with a brief explanation of the study and the patient will be asked whether the researcher may contact them by telephone. If the patient agrees, he or she will sign a specific informed consent form for telephone contact. The patient will be given a folder with an information leaflet, contact information and the informed consent form. If the patient immediately decides not to participate, the oncologist or oncological nurse asks the patient whether he/she wants to provide a reason for not participating, but the patient is not obliged to do so. If the patient has given their informed consent to be contacted by telephone, the researcher will phone the patient within one week. A meeting (in person or by telephone) will be scheduled at in which outstanding questions relating to the study can be answered, and at which the informed consent form will be signed in the presence of the researcher before the patient can participate in the study (which is known as GIRONA: GastroIntestinal cancer patients Receiving Occupational support Near and After diagnosis). The patient subsequently receives the baseline questionnaire, either on paper or digitally (depending on their preference). If they do not return the baseline questionnaire, the researcher will contact them by telephone after one week.

Participants can leave the study at any time, for any reason, without any consequences for their normal cancer care. They will be asked about their reason for withdrawal, but they will not be obliged to answer this question.

### Randomization

When the researcher has received the baseline questionnaire, the patient will be randomized to 1) the intervention group that will receive tailored work-related support, or 2) the control group that will receive care as usual. A computerized randomization programme ALEA [24] will be used to do this. As patients differ between the participating hospitals in terms of diagnosis, demographic factors and age, and because these factors are important prognostic factors for RTW [25], randomization will be stratified for gender, age (age groups: 18–54 and 55–63 years) and hospital, so as to prevent bias due to unequal randomization. Minimization will be applied to equalize group sizes. The patients, healthcare professionals and researchers will not be blinded for the group assignment.

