#### Prognostic factors

The prognostic factors include age, gender, marital status (married/single/cohabiting/widowed/divorced), education (seven categories), diagnosis (primary GI cancer diagnosis: oesophagus, stomach, liver, pancreas, biliary, small intestine, colon or rectum), treatment type (surgery, radiotherapy, chemotherapy, hormonal therapy, other) and treatment duration assessed with the self-reporting questionnaires. Fatigue is measured using the Multidimensional Fatigue Inventory questionnaire (MFI) [39], with 20 items divided into five sub-scales: general fatigue, physical fatigue, reduced activity, reduced motivation and mental fatigue. The sub-scale scores range from 4 to 20; a higher (implies 20) score indicates greater fatigue. Depression is measured using the scale developed by the Centre for Epidemiologic Studies for Depression (CES-D) [40], scored with 20 items. The scores range from 0 to 60; a higher (implies 60) score indicates greater depressive symptoms weighted for the past week. Cognitive functioning is measured with the Cognitive Symptom Checklist-Work, Dutch Version (CSC-W DV), containing 19 items, with the sub-scales for working memory and executive function. Scores range from 0 to 100, with higher scores indicating more cognitive symptoms (i.e., more limitations) in the work context. This questionnaire has been translated and a customized version of the Cognitive Symptom Checklist-Work (CSC-W) [41] validation article will be published.

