#### Primary study parameter

For the primary outcome measure (RTW), the number of days until RTW (either full or partial) will be analysed using a Kaplan-Meier survival method. The patients who dropped out of the study will be censored. The differences between the intervention and the control group will be tested using a log rank test. If significant differences between the intervention and control groups are found with regard to the prognostic variables, the outcome variable RTW will be adjusted for these variables in a multivariate Cox regression analysis. In addition to the ITT analysis aimed at ‘all—cause return to work’, the analysis will be performed excluding those patients who died during follow-up and those who have a life expectancy of less than a few months, because they will not RTW.

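### Diagnosis is named as a reason for stratifying but is not an allocation factor, and the significance-triggered Cox adjustment only partly makes up for it; the cost is modest precision, not bias

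*Protocol article*

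**What the plan says.** All references are to the protocol article.

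- **Randomization** gives the reason for stratifying: "As patients differ between the participating hospitals in terms of diagnosis, demographic factors and age, and because these factors are important prognostic factors for RTW". The rule that follows is "randomization will be stratified for gender, age (age groups: 18–54 and 55–63 years) and hospital", and its purpose is "so as to prevent bias due to unequal randomization". A separate sentence adds: "Minimization will be applied to equalize group sizes". No other list of factors is given for the minimization.
- **Study population** admits "oesophagus, stomach, liver, pancreas, biliary, small intestine, colon or rectum cancer", with "no study restrictions for type of treatment" beyond curative intent.
- **Prognostic factors** lists diagnosis again, site by site: "diagnosis (primary GI cancer diagnosis: oesophagus, stomach, liver, pancreas, biliary, small intestine, colon or rectum".
- **Statistical analysis** compares baseline data between arms by t-test or χ²-test, with significance at p ≤ 0.05.
- **Primary study parameter** tests time to RTW with a log-rank test and makes covariate adjustment conditional: "If significant differences between the intervention and control groups are found with regard to the prognostic variables", a multivariate Cox model adjusts for those variables.
- **Secondary study parameters** and **Economic evaluation** define the 12-month relative risk and a cost-effectiveness ratio built on RTW rates. Neither mentions adjustment.

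**The concern.** The reason and the rule do not match. Three characteristics are said to vary between hospitals and to matter for RTW: diagnosis, demographic factors and age. Age is stratified directly, and demographic factors are represented directly by gender. Only diagnosis, the first one named, is left to hospital. Stratifying by hospital can even out differences in case mix between centres, but it does nothing about tumour type within a centre that treats several.

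The analysis plan does not close this gap. Whether diagnosis enters the Cox model depends on a baseline significance test, so an imbalance just below the threshold is left alone however prognostic diagnosis is. At stake is the precision of the RTW comparison and how convincing a borderline result would be if the arms visibly differed in tumour mix.

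**Working it through.** The point rests on no figure in the plan. The inputs from the Sample size section are N = 310 (155 per arm) and RTW of 81% v 63%. The stated size does reproduce: a two-sided 5% test with 80% power and continuity correction gives 108 per arm, or 216, and 216/0.70 = 309. Nothing below changes that size.

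Assumptions that are not in the documents: a tumour group with a 30% share, an RTW gap between tumour groups of 10 to 40 points, six hospitals, and a biased coin of 0.8 in the minimization.

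1. **Chance imbalance if diagnosis is not balanced.** The SD of the between-arm difference in the group's share is √(p(1−p)·4/N) = √(0.3 × 0.7 × 4/310) = 5.2 points. The 95% limit is 1.96 × 5.2 = 10.2 points. For shares of 10%, 20% and 50% the limit is 6.7, 8.9 and 11.1 points.

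2. **How much hospital helps.** Minimization at N = 310 was simulated (600 runs per setting). The table gives the 95th percentile of the absolute imbalance in the 30% group:

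| Factors | Diagnosis unrelated to hospital | Share 50% in half the hospitals, 10% in the rest |
|---|---|---|
| Gender, age, hospital | about 10 points | about 9 points |
| The same plus diagnosis group | about 2 points | about 2 points |
| Diagnosis group added from patient 100 onward | about 2 points | about 2 points |

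   Even a strong link between hospital and diagnosis removes only about a point.

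3. **Effect on the RTW difference.** With a 30-point gap, the diagnosis component has SD 5.2 × 0.30 = 1.6 points, and its 95% limit is 10.2 × 0.30 = 3.1 points.

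4. **Whether that is extra error.** The standard error of the RTW difference at N = 310 is √((0.81 × 0.19 + 0.63 × 0.37)/155) = √(0.387/155) = 5.0 points. The mean outcome variance is 0.387/2 = 0.1935. Tumour group accounts for 0.3 × 0.7 × 0.30² = 0.0189 of it, or 9.8%. Removing that component multiplies the standard error by √(1 − 0.098) = 0.95, a 5% reduction. The 1.6 points are therefore already inside the 5.0, since √(5.0² − 1.6²) is about 4.7. For gaps of 10, 20 and 40 points the reduction is 0.5%, 2.2% and 9.1%.

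5. **When the Cox rule starts to act.** A two-group χ²-test at 5% reaches significance at about 1.96 × 5.2 = 10.2 points, so smaller imbalances stay unadjusted. If diagnosis is tested in its eight listed categories, the critical value on 7 degrees of freedom is 14.07. If this one contrast carried the whole difference, it would have to reach √14.07 × 5.2 = 19.5 points.

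**The case against.** The strongest reply has four parts.

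- **The text promises less than it seems to.** Its premise is that patients differ between hospitals, and stratifying by hospital answers exactly that. Balance of diagnosis within a hospital is not promised. This is fair as a reading of the premise. But the same sentence calls diagnosis prognostic in its own right, and age, which is also said to vary by hospital, is still stratified directly.
- **A reader might infer systematic bias, or an added error of about 3 points against the planned 18.** The documents support neither. Randomization balances diagnosis in expectation, and the log-rank test and confidence intervals already allow for chance imbalance, so type I error is not inflated. Step 4 shows that the 3 points are part of the standard error, not an addition to it. This objection stands in full.
- **A safeguard exists.** The Cox adjustment starts at about the imbalance that step 1 puts at the 95% limit. This stands in part. The rule is insensitive if eight categories are tested, it never acts on smaller imbalances, and it is stated for the Cox model alone.
- **The choice of allocation factors is discretionary.** This is true. It is also wrong to say that diagnosis was left out of a list of minimization factors: the article calls gender, age and hospital stratification factors and gives minimization the task of equalizing group sizes. Nor do the documents show that diagnosis is the most heterogeneous entry criterion, since treatment type is unrestricted too.

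**Conclusion.** The point holds as a matter of efficiency and of consistency between reason and rule. The article stratifies because certain factors predict RTW, and then neither balances one of them directly nor commits to adjusting for it. The consequence is avoidable chance imbalance, roughly 9 to 10 points at the 95th percentile for a 30% tumour group, against about 2 if diagnosis were an allocation factor. The attainable reduction in the standard error is about 5% under a 30-point RTW gap.

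The 30% share, the RTW gap, the number of hospitals and the coin probability are all assumptions. With a gap of 10 points the gain is negligible. The 5% refers to the difference in RTW proportions; in a Cox model the benefit of adjustment shows mainly as power, not as a smaller standard error of the log hazard ratio. The point is worth acting on because the remedy is cheap and diagnosis is known before randomization: it is checked at eligibility, and cancer type is among the baseline factors that direct patients to support type C.

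**What to change.** 1. **Main change.** Prespecify adjustment for a grouped diagnosis factor (for example colon/rectum v other GI sites), together with gender, age group and hospital, in the Cox model and in the 12-month RTW analysis, whatever the baseline comparison shows. This replaces the rule under Primary study parameter that makes adjustment depend on a significant difference. State whether the cost-effectiveness ratio uses the adjusted or the unadjusted RTW difference.
2. **Optional.** Add the same grouped factor to the ALEA minimization for the remaining patients, with the diagnoses of those already randomized entered so that the algorithm counts them.

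**Cost.** The first change needs a protocol amendment, no new data and no change in sample size. The second also needs one extra field in ALEA and, because recruitment is under way, a documented mid-trial change of the allocation scheme. A sponsor unwilling to change allocation mid-trial recovers most of the precision from the first change alone.

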### The intervention: tailored work-related support

The intervention consists of three individual meetings between a patient and a healthcare professional within the clinical setting. As work-related problems differ in severity, the intervention will be divided into three types of support, namely: support A, support B and support C.

In an earlier study (published separately) with an expert panel consisting of physicians, oncological nurses, (oncological) occupational physicians, social workers and patients, a decision diagram was drawn up that, based on a list of factors from the literature, refers the patient to one of the three types of support (A, B or C) for the tailored work-related support intervention (see Table 1). These factors have been added to the patients’ baseline questionnaire (T0). Based on a participant’s answers to this baseline questionnaire and the decision diagram, the researcher will refer the participant to the tailored types of support A, B or C.

**Table 1 Tab1:** Overview of tailored support (A, B and C), depending on type of work-related problems experienced

Healthcare professional	A (oncological nurse)	B (occupational physician)	C (multidisciplinary team)
Factors (differ according to type of support)	• Fatigue • Pain • Treatment • Uncertainty about the future • Lack of support from family and friends	• Lack of support in work environment • Neuropsychological symptoms • Occurrence of side effects that prevent patient from doing current work *Combination of the following factors:* Number of working hours—treatment—stage of cancer and fatigue	*Combination of the following factors:* Medical complications—fatigue—stage of cancer—type of cancer—perception of change regarding work—dietary problems
First meeting Points for discussion include:	• Discuss restrictions on work due to cancer • Inform patient about the importance of work • Feasibility of continuing to work during treatment • Patient’s point of view on work • Plan to RTW or sustain work	• Discuss restrictions on work due to cancer • Inform patient about the importance of work • Feasibility of continuing to work during treatment • Patient’s point of view on work • Plan to RTW or sustain work • Advice on workload/planning working hours/tasks, etc.	• Preliminary interview, occupational physician and patient • Multidisciplinary team consultation • Occupational physician provides feedback to patient • Discuss restrictions on work due to cancer • Inform patient about the importance of work • Feasibility of continuing to work during treatment • Patient’s point of view on work • Plan to RTW or sustain work • Advice on workload/planning working hours/tasks, etc.
Second meeting Points for discussion include:	• Discuss contact with work environment • Already resumed work or still working • Barriers to RTW • Discuss key decision-points within the process of reporting sick leave (legal obligations) • Evaluate aims first meeting	• Discuss contact with work environment • Already resumed work or still working • Barriers to RTW • Discuss key decision-points within the process of reporting sick leave (legal obligations) • Evaluate aims first meeting	• Discuss contact with work environment • Already resumed work or still working • Barriers to RTW • Discuss key decision-points within the process of reporting sick leave (legal obligations) • Evaluate aims first meeting
Third meeting (if indicated)	Repeat matters discussed in second meeting • Discuss contact with work environment • Already resumed work or still working • Barriers to RTW • Discuss key decision-points within the process of reporting sick leave (legal obligations) • Evaluate aims first and second meeting	Repeat matters discussed in second meeting • Discuss contact with work environment • Already resumed work or still working • Barriers to RTW • Discuss key decision-points within the process of reporting sick leave (legal obligations) • Evaluate aims first and second meeting	Repeat matters discussed in second meeting • Discuss contact with work environment • Already resumed work or still working • Barriers to RTW • Discuss key decision-points within the process of reporting sick leave (legal obligations) • Evaluate aims first and second meeting

The three support types also differ in terms of the healthcare professional providing the supportive care. The intervention will be implemented by an oncological nurse in support type A, by an oncological occupational physician (specialized in oncological patients’ RTW) in support type B, and by a multidisciplinary team (including, at a minimum, an oncological nurse, the treating physician and the oncological occupational physician) in support type C. The main differences in the three types of support within the intervention are thus the factors for which a patient is referred to support type A, B or C, and the healthcare professionals who provide the support (Table 1).

Before the start of the study, the oncological nurses who will give the work-related support in the intervention participate in a training session lasting 2.5 h. This training session will consist of an informative part on the GIRONA study, the intervention and the importance of work for patients, and training on the rights and obligations of employees on sick leave in the Dutch social security system. Furthermore, work-related problems due to cancer and cancer treatment will be discussed, such as the feasibility of continuing to work during treatment, the factors that have an impact on the RTW, and the extent to which patients are open about their cancer with colleagues and employers. In addition, the checklist forms, which serve as a guideline for conversation, are discussed and practised with reference to a case.

The training session is given by the researcher [AZ], who has clinical experience as a nurse and conducts research on cancer and work. The training session includes elements that were used in previous research, in which a work-directed intervention was developed consisting of four meetings with a nurse and a meeting with the occupational physician and supervisor to make a RTW plan [26]. The oncological occupational physicians are specialized in supporting patients with cancer who encounter work-related problems. They followed an accredited training course on ‘basic training for oncological occupational physicians’, given by the Netherlands School of Public and Occupational Health (NSPOH) in Amsterdam, the Netherlands.

The aim of the *first meeting* is to inform patients about the importance of work during and after treatment, to identify any work-related problems, and to make a plan for the RTW (Table 1). The meeting will be scheduled before the start of the treatment and will take the form of an individual face-to-face meeting lasting approximately 30 min.

The *second meeting* aims to inform and evaluate the goals of the first meeting. This meeting will be scheduled after the first meeting, in consultation with the patient and the supporting healthcare professional (depending on the diagnosis/treatment and preferences of the patient). It will take place no more than three to six months after the first meeting. It will take the form of an individual face-to-face meeting and last about 30 min (Table 1). At the end of the meeting, the healthcare professional will evaluate whether the work-related support being provided is sufficient (on the basis of the decision diagram and the patient’s answers). If the support proves to be insufficient, the type of support will be adjusted.

The *third meeting* will consider the same issues as the second meeting: evaluating the goals of the first and second meetings. This meeting will also be scheduled at the request of the patient and/or the supporting healthcare professional at the second meeting, depending on diagnosis/treatment and the preferences of the patient, and in a maximum of six to nine months after treatment (Table 1).

In the support C-type intervention (multidisciplinary meeting), the oncological occupational physician will first hold a face-to-face meeting with the patient before the multidisciplinary meeting. The team will subsequently confer to discuss the outcomes identified by the oncological occupational physician with respect to RTW possibilities and restrictions. The oncological occupational physician will lead the multidisciplinary team consultation and is designated to provide the patient with feedback in a further face-to-face or telephone meeting.

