#### Descriptive factors

The descriptive factors include breadwinner status (yes/no), job position (permanent contract/temporary contract/temporary worker/self-employed/other), employment status (employed/unemployed/self-employed/pension), years in current position, and company size (large 100 ≥ employees/medium-sized 10–100 employees/small 1–10 employees, or not applicable; self-employed), which will be assessed with the self-reporting questionnaires. The stage of cancer will be assessed from the patient’s medical records. Furthermore, the Perception and Judgement of Work (VBBA) [42] questionnaire will be used, with the sub-scale ‘physical workload’ containing seven items. The scores range from 0 to 21; a higher score indicates a higher physical workload. The importance of work is measured with a Visual Analogue Scale (VAS-scale), with a line running from 0 (not important) to 10 (most important).

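### The A/B/C class is described for the intervention group only and has no place in the analysis, although its T0 inputs are collected from everyone before randomisation; scoring all participants before allocation would be a cheap improvement.

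*Protocol article*

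**What the plan says.** All references are to the protocol article.

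- **Timing.** Randomization section: "When the researcher has received the baseline questionnaire, the patient will be randomized". T0 answers therefore exist for both arms before allocation.
- **Inputs.** The section on the intervention says of the decision-diagram factors: "These factors have been added to the patients’ baseline questionnaire (T0").
- **Use.** From those answers and the diagram, "the researcher will refer the participant to the tailored types of support A, B or C". The Abstract (Methods/Design) ties this to one arm: "the intervention group will be divided into groups receiving three types of support (A, B or C"). The article says nothing either way about classifying controls.
- **Balance.** Randomization section: "randomization will be stratified for gender, age (age groups: 18–54 and 55–63 years) and hospital". The class is not included.
- **Baseline lists.** Neither Prognostic factors nor Descriptive factors contains the class. Some components are listed for patients in general: "Fatigue is measured using the Multidimensional Fatigue Inventory questionnaire (MFI"), with diagnosis and treatment type in the same list. Stage is under Descriptive factors: "The stage of cancer will be assessed from the patient’s medical records".
- **Analysis.** The effect and cost comparisons set whole arm against whole arm. Under Primary study parameter, the Cox model adjusts for prognostic variables only where they differ significantly between arms.
- **Blinding and change of support.** Researchers know the allocation (Randomization). The type of support may be changed at the end of the second meeting (section on the intervention).

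**The concern.** The diagram was built by an expert panel to sort patients by the severity and kind of their work-related problems. That makes the class a plausible single summary of baseline outlook for return to work (RTW). It depends on information gathered before randomisation, so the initial class can be a proper baseline variable in both arms. The plan describes it only as a step in delivering the intervention.

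Two things follow.

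1. If anyone later wants the class in controls, it will be assigned after allocation, possibly after outcomes, by staff who are not blinded. Where answers fit the diagram imperfectly, that leaves room for judgement which scoring before allocation would remove.
2. The class is not on the prognostic list, and the adjustment rule acts only on prognostic variables that differ significantly. The class would therefore not enter the Cox model under the rule as written.

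The three types are delivered by a nurse, an occupational physician or a multidisciplinary team, so readers will ask how the effect varies across them. Comparing A, B and C within the intervention arm would be confounded by severity, and setting one type against all controls would not be like for like. Comparing arms within the same initial class is the fair way to look.

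**Working it through.** **1. The plan's own figure.** Inputs from Sample size: 63% v 81% RTW, 80% power, p < 0.05. Two-sided test of two proportions, pooled p = 0.72:

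- n per arm = [1.96·√(2·0.72·0.28) + 0.8416·√(0.63·0.37 + 0.81·0.19)]² / 0.18² = 96.5, so 97 (194 in total).
- With continuity correction: (96.5/4)·[1 + √(1 + 4/(96.5·0.18))]² = 107.3, so 108 per arm, **216 in total**.
- Inflation for 20% loss plus 10% mortality: 216/(1 − 0.30) = 308.6, so **309**.

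Both stated figures reproduce. Neither uses the class, so scoring it in controls changes neither.

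**2. Where the class and its components stand.**

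| Item | Recorded without restriction by arm? | Role in the article |
|---|---|---|
| Fatigue, diagnosis, treatment type | Yes | Prognostic list; Cox only if significantly different |
| Stage | Yes, from records; timing not given | Descriptive only |
| A/B/C class | Described for the intervention group only | Referral; no analysis role |

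Part of the content can reach the model through its components, but the class cannot.

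**3. What adjustment might gain.** The documents give neither class shares nor RTW gradients, so these are assumptions: 216 evaluable, split 50/30/20, exponential RTW times, 12-month RTW of 63% in controls, and a conditional hazard ratio of ln(1 − 0.81)/ln(1 − 0.63) = 1.67. The simulation compared Cox models with and without the class. The ranges are over repeated runs.

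| RTW hazards in A, B, C | Power unadjusted | Power adjusted |
|---|---|---|
| 1, 0.6, 0.35 | 83–85% | 88–90% |
| 1, 0.7, 0.5 | 86–88% | 88–89% |

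With 2,000 trials a power of 85% carries a Monte Carlo error of about 1.96·√(0.85·0.15/2000) = ±1.6 points. The gain is thus roughly 0 to 5 points, and unadjusted power stays above the planned 80%. In the steep case the unadjusted hazard ratio averages 1.61 and the adjusted one 1.68. Random allocation is intact, so this gap is the difference between a marginal and a conditional hazard ratio, not confounding.

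**4. Precision by class.** Half-width = 1.96·√[(0.81·0.19 + 0.63·0.37)/n] = 1.96·√(0.387/n), with n evaluable per arm and the planned rates in every class.

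| Class (assumed share of 216) | n per arm | 95% half-width |
|---|---|---|
| A (50%) | 54 | ±17 points |
| B (30%) | 32.4 | ±21 points |
| C (20%) | 21.6 | ±26 points |

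**5. Power by class.** For the planned 18-point difference (two-sided 0.05, no continuity correction), power within a class is 26% at a 20% share, 40% at one third and 55% at 50%. Such contrasts can only be exploratory.

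**The case against.** A reader might infer that the trial has lost a covariate, that controls have no class, or that effects by support type cannot be estimated as randomised contrasts. The documents do not support this. They are silent about controls; they do not exclude them. T0 answers are held for everyone and stage is taken from records, so the initial class can be worked out for controls at any time before analysis, blind to outcome.

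A reader might also infer that a planned analysis is confounded. None is: the article plans no comparison between support types, and its aim is to evaluate the tailored intervention as a whole. Covariate and subgroup detail is also commonly left to a full protocol or analysis plan that is not at hand.

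Further points count against making much of this.

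- Several components are already on the prognostic list.
- Coded participant numbers are meant to keep the analysis blind, although the article does not extend this to scoring the class.
- Some diagram factors, such as side effects and medical complications, may be unknown before treatment.
- Support may change at the second meeting, so the initial class does not identify the support finally received.

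All of this stands. What remains is narrow. The article does fix a prognostic list and an adjustment rule, and under them the class would not enter the model. Researchers are unblinded, so the timing of scoring matters.

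**Conclusion.** The point holds as an inexpensive improvement, not as a flaw in validity. The primary log rank comparison, the type I error and the figures 216 and 309 are unaffected. A class scored before allocation and entered in the Cox model by prior decision is somewhat better than a significance-triggered rule that leaves it out. It also permits like-for-like exploratory contrasts.

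The expected gain is small: about 0 to 5 points of power for the Cox analysis, and by-class intervals of about ±17 to ±26 points. Both results rest on the assumed 50/30/20 split of 216 evaluable patients. The first also rests on the assumed gradients, and the second on the planned 81% v 63% holding in every class. Any by-class result would concern the initial class. It should not be read as showing that a given type of support works, because the type may change.

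**What to change.** 1. Apply the decision diagram to every participant's T0 answers, with stage where it is available, before the allocation is drawn. Store that initial class for both arms and leave it unchanged if support is later adjusted.
2. Add the initial class to the list of prognostic factors. Name it as a Cox covariate in advance, whether or not it differs significantly between arms. State that the adjusted hazard ratio is conditional on class.
3. Report the treatment effect within initial class A, B and C with confidence intervals and one interaction test, labelled exploratory and described as effects by initial class.

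**Cost.** About 155 control forms to score (310/2) and one added table, with no new patient questionnaire. The article does not say when stage is abstracted, so a written rule is needed for scoring when stage or another diagram input is not yet known. The by-class estimates will be wide and must be presented as such.
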